##### Post therapy (6 months)

*Measures of attrition and engagement with therapy*: during the course of the study we expect a few participant deaths, which are likely to be random. Additionally, we will record change of residence, illness, geographical distance from therapy, did not attend rates, and the reasons for not doing so*Assessment of ‘blindness’ by rater*. At the primary endpoint of 6 months, once the BDI-II and BAI have been rated, the researcher will be asked to guess the group allocation (TAU or VIP or not sure)*Changes in prescribed psychotropic medication:* anti-depressant or anxiolytic/hypnotic medication*Other psychological treatments received*. This may include seeing a counsellor, psychotherapist or victim support counsellor and can include both statutory and privately funded provision*Measures of satisfaction with treatment* by rating on a 5-point scale (*not at all* to *very much*) whether the VIP was perceived as useful*Reason for missing follow-up (e.g. withdrew, died, etc..*

#### Timing of enrolment, interventions and measures

The timing of enrolment, allocation, collection of measures and study closeout, is summarised in the Standard Protocol Items: Recommendations for Interventional Trials (SPIRIT) diagram in Table 1.

#### Assessment of therapists’ competence and adherence to VIP manual

We encourage all therapists to digitally record their therapy sessions and a random sample of 1 in 10 recordings will be selected for quality control for competence of delivery of the therapy and adherence to the manual.

##### Therapists’ competence

Treatment quality will be rated by an accredited member of the British Association of Behavioural and Cognitive Psychotherapies expert in the field using the Cognitive Therapy Scale-Revised [39]. Each item is rated from 0 to 6 on a visual analogue scale, ranging from incompetent through to novice, advanced beginner, competent, proficient and expert. The total score ranges between 0 and 72. Therapists would be expected to achieve a minimum score of 36.

##### Adherence to the VIP manual

The use and the development of a Therapy Components Checklist (TCC) arose from previous work [27, 40] which was further developed in the HAVoC study [8]. We identified what we considered to be 26 core elements required in the delivery of the VIP. These core elements were operationalised in the treatment manual. Central to the components checklist, we wanted to ensure that the therapists adhered to the range of CBT procedures (i.e. they used a combination of cognitive, behavioural and cognitive-behavioural techniques, as well as specific issues related to our CBT intervention for victims of crime). The therapists will be asked to list the components of therapy that they have covered at the end of each therapy session. We will describe the components reported, requesting the independent assessor responsible for rating therapists’ competence to complete the TCC for the rated session and compare the therapists’ self-report with their assessors report.

##### Therapist supervision

All therapists will be asked to phone at least once a month to the group supervision taking place twice monthly. They will be asked to present their therapeutic interventions that worked well as well as identifying problem areas. They will also be able to contact the chief investigator by phone, or by email with a response within two working days, to discuss any major therapeutic difficulties.

#### Data entry and storage

Outcome data will be collected directly onto paper forms by researchers employed on the VIP trial. Each paper form will then be hand-delivered to the main trial office by the trial researcher. This data will then be entered onto the secure online Sealed Envelope database by a member of the trial team (either a trial researcher or trial administrator). A portion (10%) of all entered data will be checked against the original paper form for accuracy. At the end of the trial after database lock, the trial dataset will be downloaded from Sealed Envelope by the trial statisticians.

#### Trial monitoring

The trials Data Monitoring Committee comprises three independent members including an expert in clinical trials methodology and medical statistics, an expert in mental health, and an expert in old-age psychiatry. This Data Monitoring Committee will meet at least once a year throughout the running of the trial. A Trial Steering Committee will also meet once a year. The Trial Management Group, consisting of grant applicants, public representatives, and members of the clinical trials unit PRIMENT, will meet approximately every 3 months throughout the running of the trial. Both the Trial Steering Committee and the Data Monitoring Committee contain members who are independent of the trial, and will be able to hold closed sessions without trial members present to independently monitor the trial and make any necessary decisions on the running of the trial.

As no harm to participants is regarded as likely from CBT, the trial does not have specific interim analysis or stopping guidelines. The Data Monitoring Committee and Trial Steering Committee will have the usual power to stop the trial if they deem this necessary, as outlined in the National Institute for Health Research guidelines for trial committees.

#### Statistics

##### Power

Efficacy analysis will use changes from baseline to the end of the intervention period (6 months post crime) in a standardised combination of BAI and BDI-II scores. For standardisation, the corresponding sample mean (BAI or BDI-II) will be subtracted from the BAI or BDI-II measurement and then the resulting measure divided by the corresponding sample standard deviation (BAI or BDI-II). This will yield a standardised outcome measure to be modelled for all trial participants (whether anxious or depressed, with or without anxiety). Although there is little evidence as to what constitutes a clinically meaningful difference [41], consensus between experts in the field suggest that a change of 0.5 of a standard deviation, 3 or more on the BDI, is considered a NICE-approved clinically important change [42]. It is feasible to detect a (‘true’) average difference of at least 0.5 on the standardised joint scale with 90% power and a 5% significance level using a total sample size (*N*) of 168, with participants randomised VIP:TAU with a ratio 1:1. Applying an overall ‘cluster-adjustment’ for therapist effects, assuming a cluster-size of 8 intra-class correlation coefficient (ICC) of = 0.02 and 15% allowance for drop-out, increases this to *N* = 226. Using data from the pilot study, the ‘target’ standardised difference of 0.5 implies changes in both BAI and BDI-II of about 4 and this is valuable clinically, given the scales show that for moderate levels of symptoms the scores range from 20 to 28 and 16–25 for anxiety and depressive symptoms, respectively.

##### Clinical-effectiveness analysis

We will follow a pre-specified plan for statistical analysis and reporting which will be finalised before database lock, and in adherence with Consolidated Standards of Reporting Trials (CONSORT) guidelines.

The primary analysis will be based on available data and conducted according to the intention-to-treat principle. The mean difference in the primary outcome in the VIP group compared to the TAU group at this time point will be estimated from a mixed-effects linear-regression model with standardised BAI/BDI-II score at 6 months post crime as the response variable, and with study arm, centre and baseline standardised BAI/BDI-II score as explanatory variables. The model will account for clustering by Mind therapist in the VIP arm using a therapist-level random effect and a patient-level random effect to account for repeated measures within patients.

Participants will be classified as having either ‘anxiety’ (alone) or ‘depression’ (with or without anxiety) and randomisation will be stratified by this primary diagnosis using separate analyses, comparing TAU plus VIP vs TAU.

The primary outcome for participants in the depression stratum is BDI-II score whereas the primary outcome for participants in the anxiety only stratum is BAI score. A combined primary outcome for both strata will be created in the following manner:
BDI-II scores will be standardised by the mean and standard deviation of BDI- II score at baseline of all participants in the depression stratum irrespective of allocationBAI scores will be standardised by the mean and standard deviation of BAI score at baseline of all participants in the anxiety-only stratum irrespective of allocationThe standardised versions of BDI-II scores from the depression stratum and BAI scores from the anxiety-only stratum will then be combined into a single variable to form the primary outcome measure, used in the linear mixed-effects regression model

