### Randomisation

Participants who consent to enter the RCT and complete baseline measures (step 3 of the study, 3 months post crime) are randomised to one of two conditions: TAU or TAU plus the VIP. Randomisation is conducted by the trial administrator using a web-based randomisation service, Sealed Envelope, provided by PRIMENT Clinical Trials Unit, an independent United Kingdom Clinical Research Collaboration registered clinical trials unit. This randomisation system has been pre-populated with a randomised list provided by an independent PRIMENT statistician and uses random permuted blocks of variable size to stratify participants by their primary diagnosis (anxiety alone or depression with or without anxiety).

Attempts will be made to ensure that all researchers collecting outcome measures are kept blind to the group allocation.

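### The primary model leaves out primary diagnosis, the only randomisation stratification factor; adding it is a free improvement, and the sentence on separate analyses needs rewording

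*Protocol article*

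**What the plan says.** - **Stratification.** The Randomisation section says that the system "uses random permuted blocks of variable size to stratify participants by their primary diagnosis". The two strata are anxiety alone, and depression with or without anxiety. Study design names the same factor, and no other is given.
- **Primary model.** The Clinical-effectiveness analysis section sets a mixed-effects linear regression of the 6-month standardised score, "with study arm, centre and baseline standardised BAI/BDI-II score as explanatory variables". It adds random effects for therapist (VIP arm) and patient. Secondary outcomes use analogous models.
- **Role of the stratum.** The same section takes the BDI-II as the outcome in the depression stratum and the BAI in the anxiety-only stratum. Each is standardised by the baseline mean and SD of its own stratum, and the two are then merged into one variable for one model.
- **Separate analyses.** Between the model and the construction of the combined outcome stands the statement that "randomisation will be stratified by this primary diagnosis using separate analyses, comparing TAU plus VIP vs TAU". Its status (primary, secondary or exploratory) is not given.
- **Sample size.** The Power section sizes the trial for one pooled comparison, an "average difference of at least 0.5 on the standardised joint scale".

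**The concern.** A model normally contains the factors by which randomisation was stratified. Stratifying balances the arms on diagnosis and so makes the treatment estimate more precise. If the model has no term for diagnosis, that gain is not credited, and variation between strata is counted as residual error.

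Here the factor also fixes the measuring instrument. Centring each scale on its own stratum's baseline gives both strata a baseline mean of 0, so the baseline covariate carries no information on a difference in level between strata. The groups differ in diagnosis and in scale, and nothing in the article implies that their 6-month means will coincide on the standardised metric. At stake are the width of the confidence interval and some power.

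The sentence on separate analyses raises a second question. It does not fit a single combined outcome, and it leaves open what role the stratum-specific comparisons have.

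**Working it through.** **1. The plan's own figure.** Inputs from the Power section: effect 0.5 SD, 90% power, 5% significance (two-sided reproduces the figure), 1:1 allocation, cluster size 8, ICC 0.02, 15% drop-out.

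- Per arm: 2 × (1.960 + 1.282)² / 0.5² = 84.06, so 168.1 in total (stated: 168).
- Design effect: 1 + (8 − 1) × 0.02 = 1.14; 168 × 1.14 = 191.5.
- Drop-out: 191.5 / 0.85 = 225.3, rounded up to 226 (stated: 226).

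Both figures reproduce, for the pooled comparison only.

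**2. Effect of omitting the stratum.** The article gives no 6-month gap between strata, no baseline correlation and no stratum split. These are assumptions: equal strata, correlation 0.5, gap varied from 0 to 1.0 SD. The number analysed is 226 × 0.85 = 192. Therapist clustering is ignored.

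- With stratum, residual variance is 1 − 0.5² = 0.75 and SE = √(4 × 0.75 / 192) = 0.125.
- Without stratum, residual variance is 0.75 + gap²/4 and the model's SE = √(4 × (0.75 + gap²/4) / 192).
- Randomisation is balanced within strata, so the estimate has a true SE of 0.125 under either model. The real critical value is c = 1.96 × (model SE) / 0.125.
- Type I error is 2 × (1 − Φ(c)). Power at 0.5 SD is Φ(0.5/0.125 − c) = Φ(4 − c).

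| Gap (SD) | Model SE without stratum | c | Type I error | Power at 0.5 SD |
|---|---|---|---|---|
| 0 | 0.125 | 1.960 | 5.0% | 97.9% |
| 0.25 | 0.126 | 1.980 | 4.8% | 97.8% |
| 0.5 | 0.130 | 2.040 | 4.1% | 97.5% |
| 0.8 | 0.138 | 2.159 | 3.1% | 96.7% |
| 1.0 | 0.144 | 2.263 | 2.4% | 95.9% |

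With the stratum in the model, every row has SE 0.125, type I error 5.0% and power 97.9%.

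**3. Check by simulation** (4,000 trials per setting, linear model with and without stratum). The mean treatment estimate equalled the true effect, to within simulation error, under both models. For equal strata, type I error without stratum was about 5% at gaps of 0 and 0.25 SD, 4.0% at 0.5 SD and 1.9% at 1.0 SD. Power at the planned effect was 97.2%, 96.5% and 95.6% at gaps of 0.5, 0.8 and 1.0 SD.

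**4. Sensitivity at a gap of 1.0 SD.**

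- With strata of 30% and 70%, the added variance is 0.3 × 0.7 × 1² = 0.21 instead of 0.25. SE is 0.141 and power 96.3%.
- With baseline correlation 0, power is about 90% against 93%.
- With correlation 0 and the effective sample that the plan allows for clustering, 226 × 0.85 / 1.14 = 168.5, true SE is √(4/168.5) = 0.154 and model SE is √(5/168.5) = 0.172. Power is then about 85% against 90%. This is the least favourable case examined.

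**The case against.** **The harm is conditional and on the safe side.** The standard error is inflated only if diagnosis predicts the 6-month score after baseline adjustment, and no figure in the article shows that it does. A gap of 0.5 to 1.0 SD is one to two times the target treatment effect. At 0.25 SD or less nothing of note happens. At the planned effect, with a baseline correlation of 0.5, power stays above 90% throughout. All of this stands and limits the severity. It does not justify leaving the term out, because including it costs almost nothing.

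**Bias or false positives.** A reader might infer that the omission biases the treatment effect or makes a false claim of benefit more likely. It does neither: randomisation is balanced within strata, and the type I error falls below 5%.

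**Two primary tests.** A reader might infer from the separate-analyses sentence that the trial will be judged on two stratum-specific tests. With equal strata, each would have about 63% power (effective sample 168.5 / 2 = 84.3), and two unadjusted tests would carry a familywise error of 1 − 0.95² = 9.75%. The article does not support this reading. The same section makes the merged variable the primary outcome for one model, and the Power section sizes the trial for that comparison. Nothing calls the stratum analyses primary. The sentence is garbled, since randomisation cannot be stratified by means of analyses, and it needs only clarification.

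**Left to the SAP.** An article may leave detail to the SAP. Here, however, it lists the explanatory variables itself, and the list lacks the stratum.

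**Conclusion.** The point holds as a modest fault of efficiency and calibration. The primary model as written has no term for the one stratification factor, which also determines the outcome scale, and baseline adjustment cannot stand in for it. This rests on the baseline, within-stratum standardisation that the Clinical-effectiveness analysis section spells out.

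The estimate remains unbiased. With 192 analysed, equal strata, correlation 0.5 and no clustering, the cost is negligible up to a gap of about 0.25 SD. At gaps of 0.5 / 0.8 / 1.0 SD the SE is about 0.130 / 0.138 / 0.144 against 0.125. Type I error is about 4% / 3% / 2%, and power at 0.5 SD about 97% / 96.5% / 96% against 98%. The omission from the listed covariates is certain; the size of its effect depends on assumptions that the article cannot settle.

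The separate-analyses sentence conflicts in wording with the single combined model but does not displace it. Overall this should be fixed, as a free improvement. It does not threaten the validity of the result. Adjusting for centre, which is not a stratification factor, is not an error.

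**What to change.** 1. Add primary diagnosis, as randomised, as a fixed effect in the primary model and in the analogous secondary models. This costs one degree of freedom and leaves the sample size of 226 unchanged. A stratum-by-baseline term, allowing the two scales different slopes, is optional and costs one more.
2. Reword the separate-analyses sentence. State that the single model on the combined outcome is the only primary analysis, and that effects by diagnosis are secondary or exploratory, estimated through an arm-by-stratum interaction with confidence intervals. Note that the trial is sized only for the pooled comparison.

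The article says that the analysis plan will be finalised before database lock and that recruitment is continuing, so both changes can still be made before the outcome data are analysed. If the SAP already contains the stratum term, it is enough to bring the published description into line.

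### The primary model is valid but adjusts for only one Beck baseline per participant; pre-specifying the other, already scheduled for everyone, would probably add a little precision at almost no cost

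*Protocol article*

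**What the plan says.** All references are to the protocol article.

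- **Model.** Clinical-effectiveness analysis plans a mixed-effects linear regression of the 6-month standardised score, "with study arm, centre and baseline standardised BAI/BDI-II score as explanatory variables". Random effects for therapist (VIP arm) and for patient are added.
- **Outcome scale.** The same section says "The primary outcome for participants in the depression stratum is BDI-II score". For those with anxiety alone, BAI takes that role. Each scale is standardised by its baseline mean and SD in its own stratum, and the two are merged into one variable. The baseline covariate is the same merged variable.
- **Baseline data.** Table 1 marks both BDI-II and BAI at baseline, 6 and 9 months, with no restriction by stratum. Randomisation concerns "Participants who consent to enter the RCT and complete baseline measures", so the scores precede allocation. The section on post-therapy measures describes the blinding guess as following the rating of both scales.
- **Missing data.** The primary analysis uses available data. Supportive analyses would add predictors of missingness to the model in a sensitivity analysis, and would use multiple imputation if appropriate.
- **Timing.** The analysis plan is to be finalised before database lock. It is a separate document and is not shown.

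**The concern.** The depression stratum takes participants whether or not they are also anxious. The stratum label does not separate these two groups, and baseline BDI-II does so only indirectly. Baseline BAI measures the difference, yet the stated model does not use it. In the anxiety-only stratum the unused score is baseline BDI-II.

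If the other scale predicts the 6-month outcome beyond the own-scale baseline, including it narrows the confidence interval for the treatment effect. Drop-out may also depend on co-existing anxiety or depression. Conditioning on the other scale would then make missing-at-random easier to defend for the headline estimate itself. What is at stake is some precision and some robustness; the validity of the comparison is not in question.

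**Working it through.** **1. The plan's own figures.** Inputs from Power: "average difference of at least 0.5 on the standardised joint scale"; "with 90% power and a 5% significance level using a total sample size" of 168; "with participants randomised VIP:TAU with a ratio 1:1"; "assuming a cluster-size of 8 intra-class correlation coefficient (ICC) of = 0.02 and 15% allowance for drop-out". A two-sided test is assumed because sidedness is not stated.

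- n per arm = 2 × (1.960 + 1.282)² / 0.5² ≈ 84.1, so 168.1 in total (170 if each arm is rounded up). The stated 168 is reproduced.
- Design effect = 1 + (8 − 1) × 0.02 = 1.14, and 168 × 1.14 = 191.5, rounded to 192.
- 192 / (1 − 0.15) = 225.9, so 226. The stated figure is reproduced.

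No baseline correlation enters, so the planned power takes no credit for any covariate.

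**2. Formula for the gain.** Let r1 be the correlation of the own-scale baseline with the 6-month outcome, r2 that of the other-scale baseline with the outcome, and r12 that between the two baselines.

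- Partial correlation p = (r2 − r1·r12) / √[(1 − r1²)(1 − r12²)]
- Residual variance is multiplied by 1 − p²
- Equivalent extra participants = 192 / (1 − p²) − 192

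The document gives none of r1, r2 or r12; **all values below are assumptions**.

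**3. Gain by partial correlation.** Power uses an effective 226 × 0.85 / 1.14 / 2 = 84.3 per arm. The last column first credits the own baseline at an assumed r1 = 0.5.

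| p | Residual variance | SE | Extra participants on 192 | Power, no covariate credit (from 90.1%) | Power, own baseline credited (from 96.3%) |
|---|---|---|---|---|---|
| 0 | 0% | 0% | 0 | 90.1% | 96.3% |
| 0.10 | −1% | −0.5% | 2 | 90.4% | 96.5% |
| 0.20 | −4% | −2.0% | 8 | 91.2% | 96.9% |
| 0.25 | −6% | −3.2% | 13 | 91.8% | 97.2% |

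**4. What correlations produce these values.**

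| r1, r2, r12 | p | Fall in variance | Extra participants |
|---|---|---|---|
| 0.5, 0.4, 0.4 | 0.20/√(0.75 × 0.84) = 0.25 | 6% | 13 |
| 0.5, 0.4, 0.5 | 0.15/0.75 = 0.20 | 4% | 8 |
| 0.5, 0.4, 0.6 | 0.10/√(0.75 × 0.64) = 0.14 | 2% | 4 |
| 0.5, 0.3, 0.5 | 0.05/0.75 = 0.07 | 0.4% | 1 |
| 0.5, 0.3, 0.6 | 0 | 0% | 0 |
| 0.4, 0.45, 0.3 | 0.33/√(0.84 × 0.91) = 0.38 | 14% | 32 |

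The gain vanishes when r2 = r1 × r12, that is, when the other scale matters only through its overlap with the own scale. The last row needs the other scale to predict the outcome better than the outcome's own baseline does, together with a weak correlation between the baselines. It is an extreme and should not be used for planning.

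**5. Cost in the same units.** One extra slope costs about 1/192 = 0.5% of variance, and two cost about 2/192 = 1.0%. At p = 0.1 the net gain is therefore close to nil; at p = 0.2 most of the 4% remains.

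**The case against.** The strongest reply is that nothing here is wrong. Adjusting a response for its own baseline is standard analysis of covariance, it is valid as written, and the sample size does not rely on more. Any collected baseline measure could be proposed in the same way, and further covariates may sit in the analysis plan that is not shown. The size of the gain is wholly assumed and its range starts at zero. Supportive analyses already deals with predictors of missingness. The added term would be BAI in one stratum and BDI-II in the other, so a single shared slope is awkward. The Primary outcomes section, which assigns the two scales to depression and anxiety in turn, could even be read as one scale per diagnosis.

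Most of this stands, and it limits the point to an option. Three parts do not remove it.

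- The article states a specific covariate list for the primary model, so the comment addresses stated text and does not rest on silence.
- The missing-data provisions in Supportive analyses act only in sensitivity analyses; the headline estimate still conditions on one scale.
- The one-scale-per-diagnosis reading conflicts with Table 1. The wording is more naturally taken as saying which scale is the outcome for whom.

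The shared-slope difficulty is met by a stratum-specific slope. The other Beck scale is also a less arbitrary choice than most candidates, because it is the trial's other primary instrument and measures the co-existing symptoms that the depression stratum mixes.

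**Conclusion.** The point holds as an optional efficiency improvement. The stated model uses one Beck baseline per participant although both are scheduled for all randomised participants. Under assumed partial correlations of 0.1 to 0.25, adding the other would cut residual variance by about 1% to 6%, roughly 2 to 13 participants' worth of information on 192 analysed. The gain may be near zero if the two baselines overlap heavily.

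Three stronger readings are not supported:

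- **The primary analysis is biased or the trial underpowered without this term.** The planned model is valid, and 168 and 226 reproduce with no covariate credit.
- **A large gain is being lost.** The 14% figure comes only from an implausible corner of assumed correlations, and the document supplies none of the three.
- **Missing data are neglected.** They are addressed, though in supportive analyses only.

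The conclusion rests on Table 1 being followed as printed, and on the other scale carrying some prognostic information of its own.

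**What to change.** Before database lock, pre-specify the other Beck baseline as a further fixed covariate in the primary model: BAI in the depression stratum and BDI-II in the anxiety-only stratum. Standardise each by its own baseline mean and SD within that stratum, irrespective of allocation, and preferably allow a stratum-specific slope. Keep the model with the own-scale baseline alone as a sensitivity analysis. State in the same place that both scales are completed at baseline by every participant, so that the Primary outcomes wording cannot be read otherwise.

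The cost is one degree of freedom with a common slope or two with stratum-specific slopes, and a sentence or two in the analysis plan. No new data are needed, and the sample size does not change.
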